#### Data analysis

All analyses will be conducted on an intention-to-treat (ITT) basis. The primary analysis will be carried out by the use of generalised linear mixed models (GLMM), to test differences in outcome measures for patients and relatives between the intervention and control groups, as well as moderator effects. To investigate possible mediating factors, we will use techniques from modern causal mediation analyses. In order to take into account the trial design in which patients and relatives (level 1) are nested within treatment units (level 2), the treatment units will be included in the models as a random effect in accordance with CONSORT guidelines for cluster randomised trials [51]. Multiple imputation procedures will be used to manage missing values of individual characteristics. To assess the robustness of the findings, tests will be redone by only including the subset of patients/relatives with complete outcome data at 6 and 12 months. Tests will also be redone by only including the subset of patients/relatives who still satisfy the inclusion criteria (F20–29 diagnosis) at 12 months. To address objective six, we will investigate whether higher fidelity scores are associated with improved outcomes for patients and relatives, within the same model setup as described above.

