#### Sample size

All the outcomes of this part are secondary outcomes. With regards to sample size however, for patients we elected the ‘interpersonal relationships’-subscale from the Behavior and Symptom Identification Scale (Basis-24) (questions 4–8). This instrument covers six domains: depression/ functioning, interpersonal relationships, self-harm, emotional lability, psychosis, and substance abuse, as seen from the patient’s perspective, and has shown good reliability and validity [47]. For relatives we chose the outcome ‘experienced support’ measured with the Carer Well-being and Support (CWS) questionnaire short version 2 part B. This part measures support from the health services, as experienced by the relative, with demonstrated good reliability. However, validity for this scale was not available, due to the lack of appropriate validating measures [48]. Since we have not found comparable studies that have published data on these instruments, we decided to use a 0.5 SD improvement (medium effect) when calculating the sample size. With 80% power and 5% two-tailed significance, we would need 64 patients and 64 relatives in each arm, in a study with individual randomisation. For our cluster randomised trial, assuming an intraclass correlation coefficient (ICC) of 0.05 and having 7 clusters in each arm, we need 112 patients and 112 relatives in each arm. Calculation is done as defined for cluster randomised trials in health services research [49, 50] and the elaboration of the CONSORT statement in relation to cluster randomised trials [51, 52]. Taking into account the possibility of a 30% drop out, we need to recruit 161 patients and 161 relatives per arm.

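### The completer re-analysis named as the robustness check cannot show whether the questionnaire outcomes withstand informative drop-out

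*Protocol article*

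**What the plan says.** The Data analysis section for patients' and relatives' outcomes states that "All analyses will be conducted on an intention-to-treat (ITT) basis". The main analysis is a generalised linear mixed model with the treatment unit as a random effect; no other random effect is named. On missing data it says that "Multiple imputation procedures will be used to manage missing values of individual characteristics". For robustness, the tests are to be repeated by "only including the subset of patients/relatives with complete outcome data at 6 and 12 months". A second repeat analysis keeps only persons who still meet the F20–29 criterion at 12 months, which is a question of diagnosis and not of missing outcomes.

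The Sample size section makes the allowance for loss: "Taking into account the possibility of a 30% drop out, we need to recruit 161 patients and 161 relatives per arm". The Blinding section withholds the unit's allocation from patients and relatives only until they have agreed to take part.

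**The concern.** The completer analysis drops everyone who lacks either follow-up and refits to those who remain. It brings in no information or assumption about the people who left. It can therefore differ from the main analysis when drop-out is related to something observed, but it cannot test whether drop-out is related to outcomes that nobody saw.

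That mechanism is plausible here, although the article neither shows it nor rules it out. Participants may learn their unit's status after consent. The outcomes in question are self-reported, and the sample-size outcome for relatives is experienced support from the health services. Dissatisfaction with the service could thus be both a low score and a reason to stop answering. If the two analyses agree and this is presented as robustness, readers will credit the result with a protection that was not tested.

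**Working it through.** **Inputs (Sample size section).** Effect: "we decided to use a 0.5 SD improvement (medium effect) when calculating the sample size". Individual randomisation: "With 80% power and 5% two-tailed significance, we would need 64 patients and 64 relatives in each arm". Clustering: "assuming an intraclass correlation coefficient (ICC) of 0.05 and having 7 clusters in each arm, we need 112 patients and 112 relatives in each arm". Drop-out allowance: 30%.

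**Step 1. Reproduce the plan's figures.**
- Two-sample t-test, 0.5 SD, 80% power, 5% two-sided: 63.8, so 64 per arm.
- Persons per cluster with k = 7: m = n(1 − ICC)/(k − n × ICC) = 64 × 0.95/(7 − 3.2) = 16.
- Design effect: 1 + (16 − 1) × 0.05 = 1.75, and 64 × 1.75 = 112 per arm.
- Drop-out: 112/0.70 = 160. In whole clusters this is 23 each, and 7 × 23 = 161.

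The figures 64, 112 and 161 all reproduce. The plan thus allows for 161 − 112 = 49 persons per arm without outcome data.

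**Step 2. Standard error of the arm contrast, in SD units.** SE = sqrt(2 × 1.75/112) = 0.177.

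**Step 3. Shift from informative drop-out.** If drop-outs in one arm differ on average by delta from what the analysis implies for them, and the other arm has no such departure, the contrast is off by 0.30 × delta.
- delta = 0.1 SD: 0.30 × 0.1 = 0.03 SD.
- delta = 0.5 SD: 0.30 × 0.5 = 0.15 SD. This is 0.15/0.5 = 30% of the planned effect and 0.15/0.177 = 0.85 SE.

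Equal departures in both arms, with equal drop-out, cancel.

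**Step 4. Would the completer check reveal it?** A simulation used 7 clusters of 23 per arm, ICC 0.05, a true 12-month effect of 0.50 SD and about 30% of 12-month outcomes missing in each arm (1,500 runs per scenario, variance components held fixed). Assumptions that are not in the article: within-person correlation 0.6, a 6-month effect of 0.35 SD, random drop-out in the control arm, and the drop-out mechanisms in the intervention arm. Three analyses were compared: a mixed model on all available 6- and 12-month data with within-person correlation; the same data with only the unit as a random effect; and completers only.

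| Drop-out in the intervention arm | All data, within-person correlation | All data, unit effect only | Completers |
|---|---|---|---|
| Completely random | 0.503 | 0.503 | 0.503 |
| Driven by the observed 6-month score | 0.500 | 0.579 | 0.583 |
| Driven by the unseen 12-month score, moderate | 0.622 | 0.641 | 0.642 |
| Driven by the unseen 12-month score, strong | 0.690 | 0.720 | 0.721 |

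The Monte Carlo standard error is about 0.003. In the last two rows every analysis overstates the true 0.50. The main model with within-person correlation and the completer analysis differ by only 0.642 − 0.622 = 0.020 and 0.721 − 0.690 = 0.031. With a unit effect alone the difference is 0.001. In the second row the correlated model is unbiased and the completer check is the biased one.

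**The case against.** The strongest objection is that analyses under informative drop-out are commonly specified in a statistical analysis plan, and the one for this trial is not shown. A completer re-analysis is also an ordinary secondary check, and the article does not claim that it tests informative drop-out. This stands in part: a fuller document may name further analyses, and nothing here says that the trial has none. But the article does fix a method for assessing robustness, and the point concerns what that method can show.

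Several stronger readings are tempting and are not supported:

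- **That 30% drop-out is expected.** The article speaks of a possibility and uses it as a recruitment allowance.
- **That the check always needs a stronger assumption than the main model.** This is so if the mixed model uses all follow-ups with within-person correlation. The article names only the unit effect, and with that alone the main model behaved almost like the completer analysis.
- **That completers must be a random sample within arm.** Drop-out that depends only on covariates in the model does no harm.
- **That the two analyses must agree, or that comparing them is worthless.** A gap, such as 0.500 against 0.583, can signal that drop-out is not completely random.
- **That outcomes will certainly not be imputed.** The phrase about individual characteristics does not settle this. Standard imputation under missing at random would in any case not address unseen dependence.
- **That the completer set breaches intention-to-treat.** As a labelled supplement beside an intention-to-treat main analysis it is ordinary practice.

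The article also offers a gift card after the third questionnaire, which may keep loss below 30%.

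**Conclusion.** The point holds for the secondary outcomes of patients and relatives that rely on the 6- and 12-month questionnaires. The fidelity primary outcomes do not depend on those questionnaires, and neither do admissions, hospital days, service use and work participation, which come from national registries.

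The size of 0.15 SD rests on three assumptions: the full 30% is lost, drop-outs in one arm depart by 0.5 SD, and the other arm shows no departure. The 0.5 SD is illustrative and has no source in the article; smaller or balanced departures give proportionately less. The closeness of the two analyses under informative drop-out rests on the assumed mechanisms and correlation. That a subset of the observed data cannot test dependence on unobserved data needs none of these assumptions. This is a worthwhile improvement and not a flaw that threatens the trial's main conclusion.

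**What to change.** Keep the completer analysis as a descriptive supplement, and state that its agreement with the main model is not evidence of robustness to informative drop-out. Add one sensitivity analysis for the questionnaire outcomes:

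- Multiply impute missing 6- and 12-month scores within arm, with a cluster effect.
- Shift the imputed values by delta in the unfavourable direction, varied separately by arm, for example from 0 to 0.5 SD.
- Report the estimates over that range and the delta at which the conclusion changes.

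This needs no new data. It costs some wording in the analysis plan, a little more analysis work, and a range of results to report where a single figure would have been simpler.

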### Blinding

For obvious reasons, local clinicians and project members providing the implementation support cannot be blinded to the clinical units’ allocation status. The project’s researchers also contribute to the implementation program, and will accordingly neither be blinded. However, most of the data gathered by project members is either self-reported or retrieved from national registries, and therefore less susceptible to experimenter bias. Patients and relatives will not be informed about their clinical unit’s allocation status until after they have agreed to participate, to counteract selection bias.

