#### Data collection and outcomes

Clinicians will fill in a questionnaire with the patient’s demographic, social, and clinical data at inclusion. They will also score the Global assessment of functioning scale (GAF), split versions for symptoms and functioning [53], along with the Health of the Nation Outcome Scale (HoNOS). The latter instrument contains 12 items on a 5-point Likert-scale, assessing clinical problems and social functioning with reasonable adequacy. HoNOS has been generally acceptable to clinicians who have used it, is sensitive to change or the lack of it, showed good reliability in independent trials and compared reasonably well with equivalent items in the Brief Psychiatric Rating Scales and Role Functioning Scales [54]. Both instruments will be repeated after 12 months or upon discharge. Before starting recruitment, clinicians attended a 1.5-h long course in scoring HoNOS and GAF, to improve the reliability of these measurements. In the majority of our clinical sites, GAF was in frequent use and HoNOS was familiar to some clinicians. We choose these instruments partly because of their brevity to reduce the burden on local clinicians.

At inclusion only, relatives will provide general demographic and social data about themselves, and patients will be screened for drug and alcohol abuse with the 11-item ‘drug use disorders identification test (DUDIT) and the 10-item ‘alcohol use disorder identification test’ (AUDIT), respectively. Both self-reported instruments have shown satisfactory psychometric properties in clinical and non-clinical samples [55, 56].

Patients and relatives will fill in their respective questionnaires at inclusion, 6, and 12 months, containing the self-reported variables and instruments in Table 1. The self-reported instruments assess the psychosocial health of patient and relative, their experience of the mental health services, including shared decision-making, and the emotional climate between patient and relative. The latter is a primary target for family psychoeducation, whereas the two first domains might be affected by various degrees of improved family involvement and support. At the same time points, exposure to family psychoeducation for patients and relatives, and exposure to involvement and support measures for relatives will be reported. Adherence with medication will be monitored with a single question to the patient, relative and clinician.

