## Discussion

The cluster randomised design of the IFIP trial will help us compare implementation-, service- and client outcomes between intervention and control arm. We will not compare the effectiveness of different implementation strategies or the effectiveness of different family interventions. Rather, we seek to combine recommended clinical interventions with recommended implementation interventions and compare the results of their systematic implementation with ‘implementation as usual’ [72]. We use the term ‘implementation as usual’ rather than ‘treatment as usual’ because the project will not prevent the control clusters from improving their family involvement practices, and there are considerable incentives for them to do so. The implementation of new clinical pathways in Norwegian mental health services coincides with the implementation period of our study. These clinical pathways set standards and deadlines for documentation, diagnostic evaluations and treatments, including family involvement practices, and will probably affect both intervention and control conditions. Since we measured baseline fidelity before the clinical pathways were launched, we might be able to monitor some of these effects.

Another challenge for our study is the timing of the inclusion of relatives and patients. To avoid selection bias, it would be optimal to include them prior to the randomisation of clusters. However since the implementation of complex practices requires time, we would risk that many patients would be discharged before being exposed to the intervention. By recruiting patients and relatives in the early- and mid-phases of the implementation period, they are likely to have various degrees of exposure to family involvement practices at inclusion. We hope to monitor parts of this exposure through the questionnaires.

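### Allocation may be disclosed to patients and relatives before they complete the inclusion questionnaire, and that score may already carry some intervention effect; disclosure should wait until the questionnaire is returned.

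*Protocol article*

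**What the plan says.** All references are to the protocol article.

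- **Blinding.** Patients and relatives are not told their unit's "allocation status until after they have agreed to participate". The stated purpose is to counteract selection bias. The section also notes that self-reported data are less susceptible to experimenter bias.
- **Recruitment.** Patients and relatives are recruited after the clusters are randomised. Inclusion opens one month before the implementation start date and continues for 12 months. The reason given is that many patients are discharged after one to two years.
- **Data collection and outcomes.** "Patients and relatives will fill in their respective questionnaires at inclusion, 6, and 12 months". Exposure to family psychoeducation (patients and relatives) and to involvement and support measures (relatives) is reported at the same times.
- **Exclusion criteria.** People with more than five single-family or ten multiple-family joint sessions, or a similarly structured intervention, are excluded.
- **Discussion.** Of those recruited in the early and middle phases, the authors write that "they are likely to have various degrees of exposure to family involvement practices at inclusion", and they hope to monitor part of this through the questionnaires.
- **Sample size.** These outcomes are all secondary. For planning, "we decided to use a 0.5 SD improvement (medium effect) when calculating the sample size".
- **Data analysis.** Mixed models test differences between arms. The article does not say whether the inclusion score is a covariate, a repeated outcome or the base of a change score.

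**The concern.** No self-reported score is taken before randomisation, so the inclusion questionnaire is the only candidate for a baseline. Two things can make it depend on the arm.

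The first is knowledge of allocation. The rule protects consent and stops there. A relative who has just been told that the unit is, or is not, receiving support may answer questions on experienced support (CWS part B) differently. This is respondent bias, which the remark about experimenter bias does not address. CWS part B is also the outcome used to size the relatives' sample.

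The second is early effect. Most of the inclusion window lies after support begins. Any benefit already present at inclusion is removed in full by a change score and in part by covariate adjustment. What is at stake is the size of the estimated effect, and the power, for the patient and relative outcomes.

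**Working it through.** **1. The plan's own figures.** Inputs from Sample size: 0.5 SD; "With 80% power and 5% two-tailed significance, we would need 64 patients and 64 relatives in each arm"; "assuming an intraclass correlation coefficient (ICC) of 0.05 and having 7 clusters in each arm".

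- Two-sample t-test: 63.8, rounded up to 64 per arm.
- Fixed number of clusters k = 7: N = 64(1 − 0.05)/(1 − 64 × 0.05/7) = 112.0 per arm, or 16 per cluster. Design effect 1 + 15 × 0.05 = 1.75; effective n 112/1.75 = 64.
- Dropout: 112/0.70 = 160. Rounding up by cluster, 16/0.70 = 22.9, so 23, and 7 × 23 = 161.

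The stated 64, 112 and 161 reproduce, and this point disputes none of them.

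**2. Share of inclusion after support starts.** Let t be months from implementation start to inclusion, uniform (assumed even accrual). If the window is 12 months in all, t runs from −1 to 11 and the share is 11/12 = 92%. If the 12 months are counted from the start date, it is 12/13 = 92%.

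**3. How much effect could be present at inclusion.** The documents give no growth curve, so three are assumed, each reaching its full value at month 18 in people already in the unit's care. With t uniform on [−1, 11], let f be the mean fraction of full effect at inclusion, g the mean fraction at the 12-month questionnaire, and f/g the share lost by a change score.

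| Assumed growth | f | g | f/g |
|---|---|---|---|
| Linear from day one, t/18 | 0.280 | 0.887 | 32% |
| Quadratic, (t/18)² | 0.114 | 0.803 | 14% |
| Six-month lag, then linear, (t − 6)/12 | 0.087 | 0.830 | 10% |

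Linear row: f = (11²/2)/(18 × 12) = 0.280, and g = [(18² − 11²)/(2 × 18) + 5]/12 = 0.887. For people new to the unit, f is near zero and so is the loss.

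Covariate adjustment loses only rho × f/g, where rho is the correlation between the inclusion and 12-month scores. With rho = 0.5 (assumed), the linear case falls to 0.5 × 32% = 16%.

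**4. What that does to power.** Suppose the true 12-month difference is 0.5 SD, of which b SD is present at inclusion, with effective n 64 per arm, rho = 0.5 and the same design effect throughout. A change score estimates 0.5 − b with SD √(2(1 − rho)) = 1. Covariate adjustment estimates 0.5 − rho × b with SD √(1 − rho²) = 0.87. The unadjusted 12-month difference stays at 0.5, with 81% power.

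| b (SD) | Change: estimate, power | Adjusted: estimate, power |
|---|---|---|
| 0 | 0.50, 81% | 0.50, 90% |
| 0.05 | 0.45, 72% | 0.475, 87% |
| 0.10 | 0.40, 62% | 0.45, 84% |
| 0.15 | 0.35, 51% | 0.425, 79% |
| 0.20 | 0.30, 40% | 0.40, 74% |

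On a 0.5 SD effect, the three curves in step 3 give b of about 0.16, 0.07 and 0.05. At this rho, the adjusted analysis has more power than the unadjusted one (81%) at b = 0.10 (84%) and slightly less at b = 0.15 (79%).

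**5. Disclosure.** This needs no arithmetic. The Blinding rule sets the earliest moment of disclosure at consent, and no statement in the article places the inclusion questionnaire before it.

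**The case against.** The strongest reply is that the article does not commit to the estimator that would be biased. Data analysis names neither a change score nor the inclusion score as a covariate, and how that score enters the model is commonly left to the analysis plan. A reader might infer from the planned 0.5 SD improvement that change from inclusion is the estimand, but 64 per arm is an ordinary two-sample calculation and does not show it. This stands: the article does not establish that the effect will be understated.

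A reader might also infer that the plan does nothing about exposure at inclusion. That is not so. Exposure is recorded at inclusion, and prior psychoeducation is capped. The late recruitment is explained in Recruitment and again in the Discussion as a deliberate trade-off, and this point does not ask to change it. Participants need not receive any intervention, and the Discussion says that implementation takes time, so early exposure may be small and the one-third figure is an upper-end scenario. All of this stands.

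On disclosure, it can be said that the rule sets an earliest moment rather than scheduling anything, and that a written recruitment procedure, not shown, may already fix the order. That is fair: early disclosure is permitted, not shown to occur. But the article states the rule affirmatively, and its stated purpose leaves the measurement uncovered.

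Finally, masking only the inclusion questionnaire leaves later questionnaires open, so a reporting shift at follow-up would enter change from inclusion in full. This too stands and limits what the fix achieves. It is not a reason to let the first score be coloured as well.

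**Conclusion.** The point holds in a limited form. The disclosure rule protects selection but not the self-reported inclusion scores. Those scores may also carry some intervention effect, because about 92% of the inclusion window follows the start of support (even accrual assumed) and the authors concede likely exposure.

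If the inclusion score is used as a baseline and early exposure is beneficial, the effect can be understated: near zero for people new to the unit, about 10–14% with lagged or quadratic growth, and up to about a third with immediate linear growth and a change score. Covariate adjustment loses less, about 16% in the linear case at rho 0.5. The growth curves and rho are assumptions, not figures from the documents.

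The net direction is not determined. Reporting shifts from known allocation, and recruitment after randomisation by unblinded clinicians, can move inclusion scores either way. Only secondary outcomes are concerned: the primary fidelity outcomes have a baseline scored before randomisation and are unaffected.

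**What to change.** **Main change.** In Blinding, and in the written recruitment procedure, state that allocation is not disclosed to patients or relatives until the inclusion questionnaire has been returned. This is one line and needs no resources. It can apply only to participants not yet included, since recruitment was under way when the article was submitted, and it does not mask the 6- and 12-month questionnaires.

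**Supporting sensitivity analysis only.** Report the 6- and 12-month arm differences both with and without adjustment for the inclusion score. Include time from implementation start to inclusion with its interaction with arm; the main effect alone would not show an early effect. Use the exposure items already collected at inclusion to show how much exposure each arm had by then. The cost is analysis wording.

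The unadjusted level difference should not become the lead estimate. It gives up protection against recruitment imbalance where unblinded clinicians recruit after randomisation, and at modest early effects it also gives up power. Nor should arm differences by month of inclusion be relied on to separate early effect from imbalance: 161/12 is about 13 people per arm per month, spread over 7 clusters.
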